### Retention

To maximise retention and minimise loss to follow-up, we will make the following efforts to retain contact with study participants. There will be one text/email reminder sent if links to questionnaires/forms are not followed by participants. If participants have not followed the initial links or reminders, then study researchers will contact up to five times to offer support and collect self-report data where possible. Outcome data collection at 6 and 12 months flexibly includes electronic, phone, post and face-to-face options. Participants will also be offered reimbursement for their time (£15 shopping voucher) on completion of 12-month follow-up.

### Data analysis

We will use descriptive statistics to present the baseline characteristics of the two study groups. We will use χ^2^ tests to compare follow-up rates between the study groups, to establish whether there is differential drop out. Analysis of smoking status will be based on the intention-to-treat principle by analysing individuals according to the treatment they were allocated to regardless of compliance. Individuals for whom we do not have the primary outcome data will be assumed to have returned to smoking. Analysis of the primary outcome will be based on a logistic regression model, adjusting for the stratification variables used in the randomisation algorithm. Secondary analysis will adjust for factors known to be predictive of relapse which will be agreed with the TSC and added to the statistical analysis plan (SAP) prior to analysis. Secondary outcomes will be analysed in a similar fashion using a general linear model. Missing data patterns will be examined, and if appropriate, multiple imputation will be undertaken. The SAP is preregistered (on the Open Science Framework (OSF))—see online supplemental appendix 1. The analysis plan may include analysis suggested by the qualitative analysis, such as subgroup analysis or mediation analysis. Any analysis will be prespecified before data lock and published in the SAP prior to any data analysis.

10.1136/bmjopen-2023-076458.supp2Supplementary data

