##### Antenatal support up to birth

Usual care provision (as delivered in any given site area) will continue also to be provided to the intervention group.BabyBreathe relapse prevention leaflet.Partner/friend/relative relapse prevention leaflet—content has been designed to encourage partners/friends/relatives to support the participant to stay smoke free after delivery, and to promote active cessation for partners/friends/relatives themselves, where needed.Brief advice from a health visitor, health visiting team member or member of the research team trained to deliver the intervention (in-person, or remote). This advice is standardised and scripted following a protocol, with tailored options including positive praise for achieving smoking abstinence and brief advice about the importance of staying smoke-free. Active signposting to the BabyBreathe digital/remote elements are included in this discussion.Electronic CO testing—participants are given an iCO monitor (Bedfont) for individual use. Those in the intervention group will be encouraged to use the iCO monitor to self-monitor CO levels at any time during the study (control participants are only prompted to submit a research reading at baseline and study end).BabyBreathe website and app—these resources have been specifically developed and the app operates on both Android and iOS (iPhone) operating systems. The website and app can be accessed using a unique code. Users may input details such as the date they quit smoking, their estimated delivery date and may access self-help support, health information and advice, including innovative motivational tools, such as a health calendar and a closed online social support group, in preparation for entering the immediate postpartum period.At each subsequent health visitor contact (in-person, or remote), support for maintaining smoking abstinence will be briefly reiterated alongside usual care, where possible.

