#### Primary outcome

The primary effectiveness outcome is self-reported continuous smoking abstinence, from birth, biochemically validated by CO monitoring at 12 months postpartum, with cut-off of less than 8 ppm (ie, a reading of 7 ppm or less) for those who are not pregnant, or with a cut-off of less than 4 ppm if they are pregnant at this time point, according to the Russell standard.^27^ Adapting the Russell standard for the postpartum population, we will grant a period of ‘grace’, allowing up to five smoking lapses (a one off instance of smoking) between the birth of the baby and the 12-month follow-up, before the outcome is counted as relapse. Participants will provide CO readings electronically, using the iCO monitor (Bedfont) and study app (iCOBabyBreathe) provided at baseline. Participants will provide the REDCap database with two CO readings at entry and follow-up. The highest of the readings will be recorded. Where CO readings take place in person as part of standard care, or research visits, or when participants request help with taking a CO reading, these readings may be used.

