### Sample size

If the primary outcome (continued smoking abstinence) occurs in 25% of the control group (based on an estimated relapse rate of 75%^13^) compared with 35% of the intervention group, then we estimate that we will need 880 participants (440 per group) to have 90% power to detect this 10% between group difference at the 5% level of significance. We estimate this difference between control and intervention groups is realistic based on recent trials.^31^ Loss to follow-up or withdrawal is not considered within the sample size calculation, as all those lost to follow-up will be counted as returned to smoking, as is the usual convention in smoking cessation trials.^32^

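### Counting a missing primary outcome as smoking is neutral between arms only if abstainers in both arms return CO readings equally often, and the intervention itself may change that

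*Protocol article*

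**What the plan says.** - **Outcome.** The Primary outcome section requires self-reported abstinence from birth, with a small allowance for lapses, plus a CO reading below a cut-off at 12 months. Readings are sent electronically "using the iCO monitor (Bedfont) and study app (iCOBabyBreathe) provided at baseline". In-person readings, research visits and help on request are also allowed as sources.
- **Device use by arm.** The monitor is listed among the intervention components in the section Antenatal support up to birth. "Those in the intervention group will be encouraged to use the iCO monitor to self-monitor CO levels at any time during the study", whereas "control participants are only prompted to submit a research reading at baseline and study end". The two sections that follow give the intervention arm tailored messages for up to 12 months and further visits that encourage re-engagement.
- **Missing outcomes.** The Data analysis section fixes the rule: "Individuals for whom we do not have the primary outcome data will be assumed to have returned to smoking". The Sample size section calls this the usual convention in the field.
- **Check on loss.** The Data analysis section plans chi-squared "tests to compare follow-up rates between the study groups, to establish whether there is differential drop out". It also provides for a look at patterns of missingness, with multiple imputation where suitable, and does not say for which outcomes.
- **Bias statement.** The Blinding section concludes that the primary outcome is at low risk of bias because CO is an objective measure.

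**The concern.** The monitor has two roles: it supplies the primary outcome in both arms, and it is part of the treatment in one. A participant given it in late pregnancy must still have a working device and app more than a year later. One arm is encouraged to keep using it in the meantime. The other is asked for nothing between baseline and study end. An abstainer who sends no reading is scored as relapsed. If that happens more often among controls, the control rate is pushed down further than the intervention rate and a difference appears without any effect on smoking.

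The rule lowers absolute abstinence rates in both arms, which is why it is called conservative. That does not make it conservative for the comparison. The same outcome also drives the cost per additional sustained abstainer in the Economic evaluation section, so any distortion carries over there.

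**Working it through.** **1. The plan's own figure.** The Sample size section assumes that the outcome "occurs in 25% of the control group" "compared with 35% of the intervention group". With a two-sided 5% level, 90% power, pooled variance and no continuity correction, this gives 440 per group, 880 in total. Power at 440 per group is 90.05%. The figure reproduces exactly and is not in question.

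**2. Inputs for the bias check.** From the document: 440 per arm, 1:1 allocation, missing scored as smoking. Assumed, because the document gives no values: true abstinence π = 30% in both arms (range 25–35%), and CO return among abstainers of rc in controls and ri in the intervention arm.

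**3. False difference.** With no true effect, the observed rates are p1 = π·rc and p2 = π·ri, so the false difference is d = π·(ri − rc).

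- 80% vs 85%: p1 = 0.30 × 0.80 = 0.240; p2 = 0.30 × 0.85 = 0.255; d = 1.5 points.
- 70% vs 80%: p1 = 0.30 × 0.70 = 0.210; p2 = 0.30 × 0.80 = 0.240; d = 3.0 points.

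**4. Probability of a significant result.** This uses the pooled two-proportion test as an approximation to the planned adjusted logistic model. With p̄ the mean of p1 and p2, s0 = √[2p̄(1 − p̄)/440] and s1 = √{[p1(1 − p1) + p2(1 − p2)]/440}:

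P = Φ[(d − 1.96·s0)/s1] + Φ[(−d − 1.96·s0)/s1]

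- 80% vs 85%: s0 ≈ s1 ≈ 0.0291; P = 0.074 + 0.007 = 0.081.
- 70% vs 80%: s0 ≈ s1 ≈ 0.0281; P = 0.185 + 0.001 = 0.187.

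| CO return among abstainers (control vs intervention) | False difference | Two-sided error, π = 30% | Error, π = 25% to 35% |
|---|---|---|---|
| equal | 0 | 5% | 5% |
| 80% vs 85% | 1.5 points | 8.1% | 7.4% to 8.8% |
| 70% vs 80% | 3.0 points | 18.7% | 15.8% to 21.8% |

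If the observed control rate is instead held at the planned 25%, the same two gaps give 1.6 points (8.3%) and 3.6 points (22%).

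**5. What the chi-squared test can see.** This depends on where the gap lies. The figures below treat a returned CO reading as follow-up.

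- Gap across the whole arm: power to detect 80% vs 85% is 50%; for 70% vs 80% it is 93%.
- Gap only among the 30% who are abstinent, with everyone else followed up at the control rate: overall follow-up is 80.0% vs 0.30 × 85% + 0.70 × 80% = 81.5%, power about 9%. In the second case it is 70.0% vs 0.30 × 80% + 0.70 × 70% = 73.0%, power about 17%.

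The bias in step 3 needs a gap only among abstainers, which is where the test on overall follow-up is weakest. If follow-up is counted by any contact or self-report rather than by a CO reading, the test does not address CO return at all.

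**The case against.** The strongest reply is that the differential is assumed. No return rate appears in the document, and both its size and its direction are open. A year of prompts could also tire intervention participants. That stands, and the error rates above are conditional on it.

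Several stronger readings are tempting and are not supported:

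- **That only the intervention arm uses the monitor.** Both arms hold it and both are asked for readings at baseline and at 12 months. Only the encouraged use in between is specific to one arm.
- **That a lost device means no outcome.** The Primary outcome section allows in-person and assisted readings. The Retention section offers a reminder, up to five researcher contacts, face-to-face collection and a £15 voucher without distinction by arm. The limit is that the researcher contacts are described as collecting self-report, which cannot by itself make a participant a success.
- **That the chi-squared test is the only safeguard.** Missingness patterns are to be examined, and self-reported point prevalence abstinence and time to relapse are secondary outcomes that need no CO reading. The test also has good power against a large arm-wide gap.
- **That the multiple imputation sentence contradicts the missing-equals-smoking rule.** The primary outcome has its own explicit rule, and the scope of imputation belongs in the SAP.

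The SAP is said to be preregistered but is not shown, so the absence of sensitivity analyses from the article is no fault. Counting missing as smoking is a recognised convention and is not wrong in itself.

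**Conclusion.** The concern holds in a conditional form. The article itself states the three elements that matter: success depends on a reading from a device issued at baseline, ongoing use of that device is encouraged in one arm only, and a missing outcome is scored as failure. Any difference by arm in CO return among abstainers therefore enters the treatment effect in full, and the design gives a specific reason why such a difference may arise. Under the stated assumptions, gaps of 5 and 10 points raise the two-sided error from 5% to about 8% and 19%. The false differences of 1.5 and 3.0 points compare with a planned effect of 10 points.

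The chi-squared test cannot establish that capture is equal, and the article attaches no action to its result. The low-risk statement in the Blinding section covers how CO is measured, not whether the reading is returned. A reader might infer that the trial will be biased towards the intervention; the document does not show that. This should be fixed before analysis, but it is not a fatal fault.

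**What to change.** Keep missing-counted-as-smoking as the primary analysis, and:

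1. Send both arms the same device-and-app check shortly before 12 months, and offer the assisted-reading route equally. This helps only participants who have not yet reached 12 months.
2. Replace the chi-squared screen with the between-arm difference in CO return and its 95% confidence interval, overall and among self-reported abstainers.
3. Whatever that shows, run a sensitivity analysis that varies the missing-equals-smoking assumption separately by arm, alongside an analysis of self-reported continuous abstinence without the CO requirement. Check first whether the SAP already contains these.
4. Qualify the statement in the Blinding section: CO verification protects against misreporting by those who give a reading, not against unequal return of readings.

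The cost is one automated message to both arms, a few extra analyses and a sentence of text. The sample size and the primary rule do not change.

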#### Secondary outcomes

Secondary outcomes (table 1) measured at 6 and 12 months post partum by online self-report, or researcher follow-up, include self-reported point prevalence abstinence, self-reported time to relapse, participant-reported partner smoking status, self-efficacy (single item, self-report), Edinburgh Postnatal Depression Scale,^27^ behavioural support use (eg, support from a stop smoking service), nicotine product use, perceived stress,^28^ the Alcohol Use Disorders Test for Consumption (AUDIT-C),^29^ health related quality of life (HRQoL) using the EQ-5D-5L.^30^ Infant health outcomes (eg, minor infections requiring General Practitioner (GP) visits and more serious ill health requiring hospitalisation), participant and infant health resource use and cost-effectiveness will be measured at 12 months postpartum using a combination of GP patient records and participant self-report.

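### Time to relapse is right-censored, but the only method stated for secondary outcomes is a general linear model, which makes no allowance for censoring

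*Protocol article*

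**What the plan says.** The Data analysis section sets the primary method first: "Analysis of the primary outcome will be based on a logistic regression model, adjusting for the stratification variables used in the randomisation algorithm". It then gives one sentence for the rest, with no exception by type of outcome: "Secondary outcomes will be analysed in a similar fashion using a general linear model".

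The Secondary outcomes section lists outcomes of several types:

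- It opens with "self-reported point prevalence abstinence, self-reported time to relapse, participant-reported partner smoking status, self-efficacy (single item, self-report". Abstinence is binary, partner smoking is binary or categorical, and time to relapse is a time-to-event outcome.
- It continues with "behavioural support use (eg, support from a stop smoking service), nicotine product use, perceived stress". The two use items are probably binary or categorical, although no coding is given.
- Infant health is illustrated by "minor infections requiring General Practitioner (GP) visits and more serious ill health requiring hospitalisation". These are probably counts or yes/no items; again no coding is given.
- The depression, stress, alcohol and quality-of-life instruments are scale scores.

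Most of these are "measured at 6 and 12 months post partum by online self-report, or researcher follow-up". The article names no survival method anywhere. Cost-effectiveness has its own regression and bootstrap method in the Economic evaluation section, so the sentence does not govern it.

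**The concern.** A general linear model needs one complete numerical value per participant. Time to relapse does not supply one. A participant who is still abstinent at 12 months has only a lower bound on her relapse time, and so does one who was lost while abstinent. Faced with such data, the stated model leaves the analyst two options. One is to discard the abstainers, who are the people in whom the intervention worked. The other is to treat the last abstinent date as a relapse date.

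The sentence also conflicts with itself. Its opening words point back to a logistic model, which is not a general linear model. A reader cannot tell whether point prevalence abstinence, the secondary outcome nearest to the primary, will be reported as an odds ratio or as a risk difference.

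**Working it through.** **Inputs from the Sample size section.** "If the primary outcome (continued smoking abstinence) occurs in 25% of the control group", "compared with 35% of the intervention group", 440 per group, 90% power, 5% significance. Exponential relapse times, the loss rates and the count distributions below are assumptions; the article gives none of them.

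**1. The plan's own figure.** Two-sided comparison of two proportions, no continuity correction:
n = [1.960·√(2·0.30·0.70) + 1.282·√(0.25·0.75 + 0.35·0.65)]² / 0.10² = (1.270 + 0.826)² / 0.01 ≈ 439.2, so 440 per group and 880 in total. The stated figure is reproduced.

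**2. How many have no relapse time.** 0.25 × 440 + 0.35 × 440 = 110 + 154 = 264 of 880 (30%), plus anyone lost while abstinent.

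**3. What a linear model would estimate.** Let λ = −ln(S)/12, where S is the proportion abstinent at 12 months. Then λ₀ = 1.3863/12 = 0.1155 and λ₁ = 1.0498/12 = 0.0875 per month. The hazard ratio is 1.0498/1.3863 = 0.76.
- Abstainers entered at 12 months: the mean is (1 − S)/λ, which is 0.75 × 8.656 = 6.49 and 0.65 × 11.431 = 7.43. The difference is 0.94 months.
- Relapsers only: the mean is [(1 − S)/λ − 12S]/(1 − S), which is (6.49 − 3.00)/0.75 = 4.66 and (7.43 − 4.20)/0.65 = 4.97. The difference is 0.31 months.

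**4. Power for time to relapse, 440 per group (300 simulated trials).**

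| Analysis | No early loss | 20% early loss in both groups |
|---|---|---|
| Linear model, relapsers only | 22% | 20% |
| Linear model, censoring time used as relapse time | 90% | 84% |
| Log-rank test | 94% | 92% |

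A separate run of 2,000 trials without loss gave 21% for relapsers only and 93% for an exponential survival model.

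**5. False positives with unequal loss.** Set both groups to 25% abstinent. Give 30% of controls and 10% of the intervention group a loss time uniform over the 12 months. A participant with such a loss time contributes on average (1/λ₀)[1 − 0.75/1.3863] = 8.656 × 0.459 = 3.97 months instead of 6.49. The spurious difference is therefore (0.30 − 0.10) × (6.49 − 3.97) ≈ 0.50 months; the simulation gave 0.48. Rejection rates at a nominal 5% (300 trials):
- linear model with censoring times used as relapse times: 40%
- linear model on relapsers only: 13%
- log-rank test: 6%

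The simulation standard error is √(0.40 × 0.60/300) ≈ 2.8 percentage points for the first figure. Loss was simulated independently of relapse within each group.

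**6. Binary and count outcomes under a linear model (1,000 trials each, 440 per group).**
- 25% vs 25%: type I error 5.2%, the same as a Wald test of the log odds ratio; interval coverage 94.8%.
- 25% vs 35%: mean estimate 0.101 against a true 0.10; power 91.1% vs 91.0%; coverage 95.2%.
- 3% vs 6%: coverage 94.0%.
- Negative binomial counts: means 2 vs 2, type I error 5.0% and coverage 95.0%; 2 vs 1.5, coverage 95.8%; 0.2 vs 0.1, coverage 95.2%.

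**The case against.** The best defence is that the sentence contains a one-word slip. Given the link back to logistic regression, a generalised linear model was probably meant, and binary and count outcomes would then be covered. A model for each outcome is also something the preregistered SAP would normally supply, and the SAP is not shown here. Nothing in the article says abstainers will be dropped. If follow-up were complete, entering them at 12 months would lose little (90% against 94% power).

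Much of this stands, and it rules out several stronger readings that a reader might infer:

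- **That the stated model gives wrong estimates and intervals for binary and count outcomes.** Step 6 does not support this. At 440 per group the differences are nearly unbiased and coverage is 94% to 96%. What remains is the effect scale and the mismatch with the primary model. Whether the infant outcomes are counts at all is an assumption.
- **That entering abstainers at 12 months understates a true difference of 2.8 months.** That figure is 11.43 − 8.66, the untruncated exponential means, and it extrapolates beyond the 12 months the trial observes. The 12-month restricted mean difference is 0.94 months, which this coding recovers when nobody is lost early.
- **That no generalised linear model could analyse time to relapse.** Piecewise-exponential and discrete-time models are generalised linear models and handle censoring, but they have to be specified, and the sentence does not do so.
- **That every secondary outcome is affected.** Scale scores suit a linear model, and cost-effectiveness has its own method.

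The defence does not remove the point about time to relapse. The article does not leave the method to the SAP; it states one, and that method does not fit. If the SAP specifies something else, the two public documents disagree and the sentence still needs correcting. Complete follow-up cannot be assumed either, since the Data analysis section itself plans a test for differential dropout. The rule that missing means returned to smoking is stated for the primary outcome and supplies no relapse date.

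**Conclusion.** The point holds for time to relapse. The stated method cannot use this outcome properly. Discarding abstainers cuts power to about 22%, against about 94%. Treating censoring times as relapse times is acceptable only with complete follow-up and can produce false positives when loss differs between groups (about 40% in the scenario tested). The two power figures rest on exponential relapse times matched to the planning rates. The 40% also rests on an assumed loss of 30% versus 10%, which is not in the article; smaller imbalances would do less harm, and with no early loss the rate was about 5%. The log-rank comparison assumes that loss is unrelated to relapse within each group.

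For binary outcomes the fault is lesser: an unclear effect scale and a sentence that contradicts its own reference to logistic regression. The primary analysis and the sample size of 880 are not affected.

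**What to change.** Replace the sentence on secondary outcomes in Data analysis with one that assigns a model by outcome type, and make the SAP agree:

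- **Time to relapse:** a censoring-aware model, with participants still abstinent censored at 12 months and those lost while abstinent censored at last contact. Cox regression would serve if a relapse date is collected. If relapse is known only to fall between two follow-ups, use an interval-censored or discrete-time model.
- **Binary outcomes:** logistic regression, as for the primary outcome.
- **Infant health and other events:** a count model if they are recorded as counts, logistic regression if recorded as yes/no.
- **Scale scores:** the linear model, and only here.
- **All models:** adjusted for the stratification variables.

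This is a change of wording before data lock. It needs no new data and no more participants.

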### Randomisation

Completion and submission of the baseline measures will trigger randomisation (see trial flow diagram, figure 1). Participants will be individually randomised in a 1:1 ratio to the control or intervention groups using a computerised web-based randomisation system managed and accessed only by Norwich Clinical Trials Unit, to ensure adequate sequence generation and allocation sequence concealment. The randomisation system will stratify by recruitment hub, partner smoking status (partner smoking and partner non-smoking/no partner) and time of quit (before or during pregnancy), as these factors are likely to predict relapse.

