The main outcome measure used in the economic analysis will be the study’s primary outcome measure, continuous postpartum smoking abstinence. This will form a cost-effectiveness study looking at cost per additional sustained abstainer. Additionally, we will use EQ-5D-5L^30^ values obtained from participants to undertake a cost utility analysis (ie, cost per QALY) estimating quality-adjusted life years (QALYs), obtained at baseline, 6 and 12 months postpartum. EQ-5D-5L questionnaires will be valued using the most appropriate scoring algorithm at time of analysis. Currently, this would be the UK mapped scores.^33^ Cost and effectiveness data will be estimated using regression-based methods to allow for differences in baseline characteristics between groups. Non-parametric bootstrapping will be used to allow for uncertainty and this will also be used to construct a cost-effectiveness acceptability curve, which shows how likely the intervention is to be cost-effective at different monetary values of the effectiveness measures. A health economics analysis plan will be agreed and published on the OSF before any analysis of health economics data.

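### As worded, the secondary-outcome model leaves out the baseline score of scales measured at baseline, which costs precision but does not cause bias

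*Protocol article*

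**What the plan says.** Under Data analysis, the article sets the primary model: "Analysis of the primary outcome will be based on a logistic regression model, adjusting for the stratification variables used in the randomisation algorithm". The Randomisation section names those variables: "The randomisation system will stratify by recruitment hub, partner smoking status (partner smoking and partner non-smoking/no partner) and time of quit" (before or during pregnancy). None of them is a baseline scale score.

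Data analysis then names one further adjustment: "Secondary analysis will adjust for factors known to be predictive of relapse which will be agreed with the TSC". It goes on directly to the remaining outcomes: "Secondary outcomes will be analysed in a similar fashion using a general linear model". No covariate list for the secondary models follows. The section refers to a preregistered SAP in a supplement, which was not available for this review.

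The Secondary outcomes section lists several scales measured at 6 and 12 months: self-efficacy (a single item), the Edinburgh Postnatal Depression Scale, perceived stress, AUDIT-C, and "health related quality of life (HRQoL) using the EQ-5D-5L". For the EQ-5D-5L, the Economic evaluation section confirms a baseline measurement: "estimating quality-adjusted life years (QALYs), obtained at baseline, 6 and 12 months postpartum". Table 1 marks ten rows at baseline, 6 months and 12 months, but the row labels are not legible in the text reviewed. The Randomisation section makes submission of the baseline measures the trigger for randomisation, so these scores predate allocation.

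**The concern.** The secondary model is defined by pointing to the primary one, and the primary is a poor template for a scale score. Everyone has stopped smoking at entry, so smoking status has no baseline variation to adjust for. A depression or quality-of-life score does vary at baseline, and its own earlier value is usually among its strongest predictors.

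Neither covariate set that the article describes is built to include that value. The first is hub, partner smoking and time of quit. The second is chosen to predict relapse to smoking, not depression, stress, alcohol use or quality of life.

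What is at stake is the width of the confidence intervals for these scales. In any single trial, a chance imbalance in the baseline score would also carry through into the estimate, although it averages out over randomisations.

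**Working it through.** **The plan's own figure.** The Sample size section gives 25% v 35% abstinence, 90% power, 5% level and 440 per group. The two-sided pooled formula without continuity correction is

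n = [1.960 × √(2 × 0.30 × 0.70) + 1.2816 × √(0.25 × 0.75 + 0.35 × 0.65)]² / 0.10² = (1.2702 + 0.8256)² / 0.01 = 439.2,

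which rounds up to 440 per group, or 880 in total. The figure reproduces. It concerns the primary outcome only, and nothing below alters it.

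**Inputs for the scale outcomes.**
- 440 per group with 1:1 allocation (Sample size; Randomisation).
- r, the correlation between baseline and follow-up score that remains after the stratification variables. The article gives no value, so 0.3 to 0.6 is assumed.
- Outcome in SD units, because no SDs are given.

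**Formulas.** Adding the baseline score multiplies the variance of the treatment effect by 1 − r² and its standard error by √(1 − r²). The equivalent sample size is 880 / (1 − r²). The difference detectable with 90% power is (1.960 + 1.2816) × √(2/440) × √(1 − r²).

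| r (assumed) | Variance factor | SE factor | SE reduction | Equivalent N | Detectable difference (SD) |
|---|---|---|---|---|---|
| no baseline term | 1 | 1 | – | 880 | 0.219 |
| 0.3 | 0.91 | 0.954 | 5% | 967 | 0.208 |
| 0.4 | 0.84 | 0.917 | 8% | 1,048 | 0.200 |
| 0.5 | 0.75 | 0.866 | 13% | 1,173 | 0.189 |
| 0.6 | 0.64 | 0.800 | 20% | 1,375 | 0.175 |

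**Power.** For an assumed effect of 0.2 SD with complete data, power is 84% without the baseline score. It is 88% at r = 0.3 and 93% at r = 0.5. At r = 0.6, 0.2 / (0.0674 × 0.8) − 1.96 = 1.75, which gives 96%.

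The rule that missing means smoking protects only smoking status, so the scales will lose participants. With 20% of scale data missing (assumed; 352 per group), power is 76% without the baseline score, 79% at r = 0.3 and 87% at r = 0.5. The proportional SE reductions do not change; the equivalent N scales down with the number observed.

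**Check by simulation.** Linear models were fitted to 400 simulated trials of 880 with no true effect, with and without the baseline score, both including two stratification factors. The ratio of mean standard errors was 0.954 at r = 0.3 and 0.867 at r = 0.5, in line with √(1 − r²). The mean estimated effect was within 0.004 SD of zero in both models, so leaving out the baseline score does not bias the estimate.

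**Outcomes outside the point.** Point-prevalence abstinence has no baseline variation, since all are abstinent at entry. Time to relapse has no baseline value.

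**The case against.** The strongest objection is that this is SAP content. The article is a summary, a SAP is preregistered, and covariates for each secondary model are commonly left to it. The sentence contains no closed list and does not exclude a baseline score. It also follows the sentence on further adjustment, so it may refer to the whole scheme and not only to the stratification-adjusted model. This stands in part: the article does not show that precision will be lost, only that it will be if the SAP follows the article's wording. It does not dispose of the point, because the article does more than stay silent. It states a model by reference to another model, and neither adjustment set it names is designed for these scales.

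The size is also open to challenge. Baseline is taken from 26 weeks of pregnancy and follow-up is 6 and 12 months after birth, so the correlation may be modest. At r = 0.3 the gain is only 5%. That is fair, and it is why a range is shown.

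A reader might also infer three stronger things that the document does not support:
- **That 6 and 12 months are analysed separately.** Nothing in the article says so. Naming a general linear model in one line does not settle how the two visits are handled.
- **That the economic section contradicts the effectiveness section.** The economic analysis uses "regression-based methods to allow for differences in baseline characteristics between groups", but it covers costs, sustained abstinence and QALYs, has its own analysis plan, and does not specify baseline utility. Different analyses need not share covariates.
- **That all the scales are shown to have a baseline.** Only the EQ-5D-5L is named as such. For the others it rests on Table 1 rows whose labels could not be read.

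**Conclusion.** The point holds as a free improvement to the model as worded. Taken literally, scales with a baseline measurement are compared without it, and their standard errors are larger than they need be. Adjustment would cut them by about 5% to 20% for an assumed correlation of 0.3 to 0.6. The conclusion depends on that assumed range, on the SAP not already including baseline scores, and, beyond the EQ-5D-5L, on baseline collection that is probable and not confirmed.

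It would go too far to say that the plan adjusts for stratification variables only, or that precision has been thrown away: the article does not say the first, and the unseen SAP could rule out the second. The issue is efficiency, not validity, and it touches no part of the primary analysis. Its priority is modest.

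**What to change.** First check the SAP and the labels in Table 1. Unless the SAP already says so, add one sentence: each continuous secondary outcome that was also measured at baseline is analysed in a linear model with its own baseline score and the stratification variables as covariates.

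Fitting 6 and 12 months jointly in a repeated-measures model, so that 6-month data inform missing 12-month values, is a reasonable option but not needed to resolve this point.

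The cost is wording only. The baseline forms are submitted before randomisation, so no further data are needed. Data analysis allows analyses to be prespecified up to data lock, so the change should be made before then.
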